**17.2 Statistical Analysis**

Descriptive statistics were generated for all patients and stratified by treatment arm for baseline patient, tumour and treatment characteristics and stratified by treatment arm for HRQOL endpoints stratified by follow-up visit, compared using the chi-square test, Fisher’s exact test, two-sample t-test, Wilcoxon rank sum test or paired t-test (compared to baseline only) as appropriate. Univariable Cox proportional hazards regression was performed for OS and DFS for all eligible variables for all patients (Supplemental Table 1 online). Kaplan-Meier estimates were generated for OS and DFS for all patients and stratified by treatment arm compared using the stratified log-rank test stratified by clinical nodal status (N0, N1). All statistical analysis was intention-to-treat and performed using SAS version 9.4 software (SAS Institute, Cary, NC, USA) using two-sided statistical testing at the 0.05 significance level. The trial was not powered to detect differences in the secondary outcomes including survival. There was no imputing, deletion, guessing, or substitution used for missing values. There were no interim analyses. There was no blinding of patients, investigators, or data analysts to the treatment allocation.

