**5.0 Research Design and Methods**

**5.1 Eligibility Criteria**

5.1.1 Histologically documented squamous cell carcinoma or adenocarcinoma of the thoracic esophagus (> 20 cm from the incisors) or gastroesophageal junction are included. Cancers of the cervical esophagus (< 20 cm are excluded).

5.1.2 No distant metastases (M0).

5.1.3 Patients will be stratified by stage (clinical N0 versus clinical N1), and surgeon (RI versus RM versus DF)

5.1.4 Patients with tumours within 3 cm distal spread into gastric cardia as detected by esophagogastroscopy. Tumours that have > 3 cm of spread into cardia of the stomach are considered gastric cancers and are ineligible.

5.1.5 Patients with biopsy (by endoscopic ultrasound, laparoscopy, or laparotomy) proven metastatic supraclavicular nodes are ineligible.

5.1.6 Patients with biopsy proven metastatic celiac nodes are ineligible. Resectable mediastinal nodes are eligible.

5.1.7 No prior chemotherapy for this malignancy.

5.1.8 No prior radiotherapy that would overlap the field(s) treated in this study.

5.1.9 Patients with other malignancies are eligible only if > 5 years without evidence of disease or completely resected or treated non-melanoma skin cancer.

5.1.10 Age > 18 years and able to tolerate tri-modality therapy at the discretion of the treating thoracic surgeon, medical and radiation oncologists. Tumours must be resectable after assessment by the thoracic surgeon.

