**7.0 Randomization**

With the completion of investigations and staging and the receipt of the baseline data recorded on the Eligibility Visit data collection forms the patient's eligibility will be re-checked and if the patient meets the inclusion and exclusion criteria, the patient will be randomized to one of two treatment groups. Blinded and blocked randomization will be in a 1:1 allocation ratio between treatment arms with stratification by surgeon. Randomization will occur centrally (Thoracic Clinical Trials Office) to ensure concealment of the process. Once randomized, the patient will be followed until death or the end of the study (1 year) and all outcome events will be attributed to the study group to which the patient has been assigned (intent-to-treat-analysis). Follow-up after 1 year will continue as per usual standard clinical practice. No clinical trial tests will be administered.

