**17.0 Sample Size Determination**

**17.1 Sample Size**

The sample size is based on an improvement in the quality-of-life as measured by the FACT-E at one year. If we assume an improvement in the treatment arm of 15 points, 2- sided α=0.05, β= 0.2 and σ=25 (28)

Formula:

n per group = (Z_α_ + Z_β_)^2^ *2σ^2^

Δ^2^

σ=25

Δ=15

n=44 per arm.

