**Summary of Sample Size Estimates**

| **σ** | **Δ** | **α** | **β** | **n**  **(each arm)** | **Add 10%** | **Total N** |
| --- | --- | --- | --- | --- | --- | --- |
|  |  |  |  |  |  |  |
| 25 | 10 | 0.05 | 0.2 | 98 | 108 | 216 |
| 25 | 15 | 0.05 | 0.1 | 58 | 64 | 128 |
| **25** | **15** | **0.05** | **0.2** | **44** | **48** | **96** |
| 25 | 20 | 0.05 | 0.1 | 33 | 36 | 72 |
| 25 | 20 | 0.05 | 0.2 | 25 | 27 | 54 |
| 25 | 25 | 0.05 | 0.1 | 21 | 23 | 46 |
| 25 | 25 | 0.05 | 0.2 | 16 | 17 | 34 |

The sample size was estimated based on an improvement in the HRQOL as measured by the FACT-E at one year of 15 points in the Neoadjuvant arm compared to the Adjuvant arm. Based on a two-sample t-test, using 2-sided testing, alpha = 0.05, power = 80% and standard deviation = 25, 48 patients would be required in each arm (96 total patients) after adjusting for 10% lost to follow-up (32). The randomization was completed according to a computer-generated randomization list by an independent statistician who had no clinical involvement in the trial and then allocated by the Thoracic Clinical Trials office to ensure concealment of the randomization process (33). Patients were randomized in a 1:1 allocation ratio and stratified by nodal status and surgeon.

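### The between-arm FACT-E test in 17.2 uses neither baseline FACT-E nor the randomization strata, which forgoes available precision; separately, 7.0 names different strata from 5.1.3, 17.1 and the schema

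*Protocol*

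**What the plan says.** **The test.** Protocol 17.2 lists the comparisons for baseline characteristics and for quality of life by visit as chi-square, Fisher's exact, "two-sample t-test, Wilcoxon rank sum test or paired t-test (compared to baseline only) as appropriate". It names no covariate or stratum for FACT-E. The sample size in 17.1 rests on the same kind of test: "Based on a two-sample t-test, using 2-sided testing, alpha = 0.05, power = 80% and standard deviation = 25".

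**The baseline score.** FACT-E is measured at the eligibility visit before randomization (6.3), and then every two months to one year (12.1).

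**The strata.** The protocol describes them in four places:

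- 5.1.3: "Patients will be stratified by stage (clinical N0 versus clinical N1), and surgeon"
- 7.0: "1:1 allocation ratio between treatment arms with stratification by surgeon"
- 17.1, below the sample size table: "stratified by nodal status and surgeon"
- Study schema: nodal status and surgeon

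For survival, 17.2 stratifies the log-rank test by clinical nodal status and does not use surgeon.

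**The concern.** In a trial of 96 patients the baseline value of the outcome is a natural source of extra precision. It is measured on the same scale and is unaffected by treatment. Section 17.2 uses it only to compare patients with themselves, so any chance difference between arms at baseline passes into the estimated treatment effect in proportion to the correlation between baseline and one-year scores.

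Stratified randomization balances the arms on the strata. If those strata predict the outcome, an analysis without them leaves their variation in the residual and overstates the standard error. The plan carries one factor into the log-rank test but none into the primary comparison.

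The conflict over the strata matters for a different reason. Until it is resolved, a reader cannot tell which factors an adjusted model should contain.

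**Working it through.** **Inputs from the protocol (17.1).** Difference 15 points ("If we assume an improvement in the treatment arm of 15 points"); "2- sided α=0.05, β= 0.2 and σ=25"; 44 per arm; 48 per arm and 96 in total after allowing for 10% loss.

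**Inputs assumed.** The correlation ρ between baseline and one-year FACT-E, the share of FACT-E variance explained by the strata, and a block size of 4. The protocol gives none of these.

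**1. The plan's own figure.** n per arm = 2σ²(z₀.₉₇₅ + z₀.₈₀)²/Δ² = 2 × 625 × (1.960 + 0.842)²/225 = 43.6, so 44. Adding 10% gives 44 × 1.1 = 48.4, stated as 48. The figure reproduces. Power of the unadjusted t-test at 44 per arm is 0.804 by the normal approximation and 0.795 by noncentral t. Design and analysis match, so there is no shortfall against the plan.

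**2. Baseline adjustment.** Residual SD = 25√(1 − ρ²). The standard error of the difference is that SD × √(2/44), and the 95% half-width is 1.96 times the standard error.

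| ρ (assumed) | Residual SD | Standard error | Half-width | Power, noncentral t | Power, normal |
|---|---|---|---|---|---|
| unadjusted | 25.00 | 5.33 | 10.45 | 0.795 | 0.804 |
| 0.3 | 23.85 | 5.08 | 9.97 | 0.831 | 0.839 |
| 0.5 | 21.65 | 4.62 | 9.05 | 0.895 | 0.901 |
| 0.7 | 17.85 | 3.81 | 7.46 | 0.974 | 0.976 |

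Spending one degree of freedom on the covariate does not change these figures to three decimals. By the normal approximation, the number per arm for 80% power would be 40, 33 and 23 at the three correlations, against 44 unadjusted.

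**3. Chance imbalance at baseline.** If the baseline SD is also 25 (assumed), a baseline difference of one standard error is 5.33 points. It shifts the unadjusted one-year difference by about ρ × 5.33, which is 1.6, 2.7 or 3.7 points at ρ = 0.3, 0.5 or 0.7. ANCOVA removes this shift.

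**4. Leaving out the strata.** This was simulated with 88 patients, six equally likely strata (two nodal categories by three surgeons), permuted blocks of 4, total SD 25 before the treatment effect, ρ = 0.5 within strata, and 8,000 runs per setting.

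| Variance explained by strata (assumed) | Unadjusted SE ÷ true SE | Type I error, unadjusted | Power, unadjusted | Power, strata and baseline in model |
|---|---|---|---|---|
| 0% | 1.00 | 4.8% | 0.79 | 0.89 |
| 5% | 1.03 | 4.3% | 0.81 | 0.91 |
| 10% | 1.05 | 4.0% | 0.81 | 0.92 |
| 20% | 1.11 | 3.0% | 0.82 | 0.95 |

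The error is in the conservative direction and disappears if the strata do not predict FACT-E. With the strata in the model, type I error stayed close to 5%.

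**5. The strata side by side.** All four places agree on surgeon. Three add nodal status, and 7.0 does not. No calculation applies; the text is inconsistent.

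**The case against.** **The test is valid and matches the sizing.** This stands. The trial was sized for an unadjusted t-test and gets about 80% power from it. A reader might infer that the reported standard errors would be wrong, or that the trial would not be analysed as randomized. The protocol supports neither. The standard error is too large only if nodal status or surgeon predicts FACT-E, which the protocol does not state, and then the error is conservative. Sections 7.0 and 17.2 both commit to intention-to-treat.

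**The gain is assumed.** This also stands. The baseline score precedes all treatment, while the one-year score follows surgery and, for many patients, chemoradiation, so the correlation may be low. At 0.3 the gain is under four percentage points.

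**Section 17.2 might mean change scores.** It does not say, and 4.1 describes the 15-point important difference relative to baseline. A change-score test would use baseline, but its SD is 25√(2(1 − ρ)). By the normal approximation at 44 per arm, power is then 0.66, 0.80 and 0.95 at ρ = 0.3, 0.5 and 0.7. ANCOVA does better at each of these values, so the recommendation is the same under either reading.

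**Covariates can be left to the SAP.** In general they can. Here the protocol itself names the test, so the choice is open to comment.

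**The strata conflict changes no standard error.** Correct. A reader might link it to lost power, but it is a separate matter of consistency.

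**The log-rank test should use both factors.** This does not follow. Two nodal categories by three surgeons gives six cells in 96 patients, for an outcome that 17.2 says is not powered. Stratifying by nodal status alone is defensible.

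**Conclusion.** The point holds as a recommendation on efficiency together with one textual inconsistency. The planned comparison is valid and delivers about the planned 80% power at 44 evaluable patients per arm. It forgoes precision that the collected data could supply. Adjusting for baseline would raise power from 0.795 to 0.831, 0.895 or 0.974 and shorten the 95% half-width from 10.45 to 9.97, 9.05 or 7.46 points, for assumed correlations of 0.3, 0.5 or 0.7. Leaving out the strata makes the standard error about 3 to 11% too large if they explain 5 to 20% of FACT-E variance, and has no such effect if they explain none. These sizes depend on values the protocol does not give; the direction of the baseline gain holds for any correlation large enough to outweigh one lost degree of freedom.

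Independently, 7.0 contradicts 5.1.3, 17.1 and the schema on whether nodal status is a stratification factor.

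**What to change.** - In 17.2, make the primary between-arm FACT-E comparison an ANCOVA at one year, the time point used for the sample size, with arm, baseline FACT-E and the randomization strata (clinical nodal status and surgeon). Keep the unadjusted two-sample test as a sensitivity analysis.
- Sections 17.1 and 17.2 are partly written in the past tense. If outcome data have already been analysed, label the adjusted model as added after the fact.
- Reconcile 7.0 with 5.1.3, 17.1 and the schema so that one set of strata, matching what was actually done, appears throughout. The model should carry that set.
- The log-rank test may stay stratified by nodal status.

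The cost is wording and a few lines of analysis code. Baseline FACT-E and the strata are already known at randomization, so no extra data or patients are needed. The model spends about four degrees of freedom: one for baseline, one for nodal status and two for three surgeons.

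### Section 17.2 names only an unstratified univariable Cox model for OS and DFS but compares the arms with a nodal-stratified log-rank test; surgeon, also a randomization factor, is in neither

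*Protocol*

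**What the plan says.** Section 17.2 describes two survival analyses.

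- A regression screen: "Univariable Cox proportional hazards regression was performed for OS and DFS for all eligible variables for all patients". It goes to a supplemental table. No strata or covariates are named, and treatment arm is not singled out.
- The arm comparison: "Kaplan-Meier estimates were generated for OS and DFS for all patients and stratified by treatment arm compared using the stratified log-rank test", with clinical nodal status as the only stratum.

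The randomization strata are stated in four places. Section 5.1.3 and the Study Schema give nodal status and surgeon. So does the text under Summary of Sample Size Estimates in 17.1: "Patients were randomized in a 1:1 allocation ratio and stratified by nodal status and surgeon". Section 7.0 gives surgeon alone: "Blinded and blocked randomization will be in a 1:1 allocation ratio between treatment arms with stratification by surgeon".

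On the standing of these endpoints, 17.2 adds: "The trial was not powered to detect differences in the secondary outcomes including survival".

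**The concern.** The protocol treats nodal status as prognostic. Section 1.0 lists nodal involvement among the reasons for poor survival, and 17.2 makes it the log-rank stratum. Yet the only hazard model named leaves it out. Any arm hazard ratio produced under this text would be univariable, while the arm p-value would be nodal-stratified.

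Two consequences follow if arm is one of the Cox variables. Leaving out a prognostic factor moves the hazard ratio toward 1 when there is a true effect. The confidence interval and the p-value can also fall on opposite sides of 0.05. In a trial not powered for survival, the estimate and its interval are what a reader will use, so a significant p-value beside an interval covering 1 would be awkward to report. It would also leave room to choose the model after seeing the data.

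**Working it through.** **The plan's own figures.** The protocol gives no target HR, event count or power for OS or DFS. Its only sample-size figure is for FACT-E: (1.96 + 0.84)² × 2 × 25² / 15² = 7.84 × 1250 / 225 = 43.6, so 44 per arm; 44 × 1.1 = 48.4, stated as 48. It reproduces. Here it supplies only the 96 patients.

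**Inputs from the protocol.** 96 patients, 1:1 (17.1); events followed to 60 months (12.1); two-sided 0.05 (17.2); 60% node-positive, from the figure of up to 60% of presenting patients in 1.0, so an upper value; allocation balanced within nodal status (5.1.3, 17.1, schema).

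**Assumptions not in the protocol.** Exponential survival; median 40 months in N0 controls; N1-versus-N0 HR of 1, 1.5, 2 or 3; true arm HR of 0.60 or 1. There were 4,000 simulated trials per setting.

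**Formulas.** At each event, let n1 and n0 be the numbers at risk in the two arms and x the arm of the patient with the event. With p = n1·e^β / (n1·e^β + n0), the Cox estimate solves Σ(x − p) = 0 and its SE is 1/√Σp(1 − p). The log-rank z is Σ(x − p)/√Σp(1 − p) at β = 0. The unstratified model counts n1 and n0 over everyone at risk; the stratified model counts them within nodal stratum.

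**True arm HR 0.60:**

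| Nodal HR | Mean events | HR, unstratified | HR, stratified | SE, unstratified | SE, stratified | Cox Wald v stratified log-rank disagree at 0.05 | of which log-rank significant, CI includes 1 |
|---|---|---|---|---|---|---|---|
| 1 | 53 | 0.594 | 0.594 | 0.281 | 0.282 | 2.1% | 1.3% |
| 1.5 | 62 | 0.607 | 0.601 | 0.260 | 0.261 | 3.7% | 2.9% |
| 2 | 67 | 0.611 | 0.593 | 0.248 | 0.250 | 7.5% | 6.4% |
| 3 | 73 | 0.642 | 0.592 | 0.237 | 0.241 | 15.4% | 14.6% |

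The averages in 96 patients sit slightly low in both columns. In large samples the stratified HR settles at 0.60, and the unstratified one at about 0.62 (nodal HR 2) and 0.65 (nodal HR 3). Disagreement varies a little between repeat runs, up to 16% at nodal HR 3.

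**True arm HR 1:**

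| Nodal HR | Unstratified model SE | Its actual sampling SD | Unstratified Wald rejects | Stratified log-rank rejects | Disagree |
|---|---|---|---|---|---|
| 1 | 0.255 | 0.258 | 5.1% | 5.4% | 0.6% |
| 1.5 | 0.240 | 0.236 | 4.6% | 5.2% | 1.1% |
| 2 | 0.232 | 0.220 | 4.1% | 5.0% | 1.9% |
| 3 | 0.225 | 0.199 | 2.7% | 5.2% | 3.2% |

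Both models average an HR of 1.00.

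**Reading the two tables.** The unstratified SE is never larger on average than the stratified one; the mean ratio runs from 0.98 to 1.00. It exceeds only the estimator's own sampling SD: 0.232/0.220 = 1.05 at nodal HR 2 and 0.225/0.199 = 1.13 at nodal HR 3. That excess depends on allocation being balanced on nodal status.

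**Adding surgeon.** Two nodal levels and three surgeons make six strata. In a companion simulation the SE rose from 0.226 to 0.233, and 0.233/0.226 = 1.03; the cost is about 2% to 3%.

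**The case against.** The strongest reply is that 17.2 never presents the Cox model as the treatment-effect analysis. The arm comparison belongs to the Kaplan-Meier curves and the stratified log-rank test, and the Cox sentence describes a screen of variables. A reader might infer that the reported treatment effect is the univariable HR, shown beside the log-rank p-value. The text does not say so, and the analysis plan, not shown here, may name another model. This stands, so the numbers above are conditional on arm being in the screen. What remains is that the protocol fixes both methods and they do not match. If arm is not in the screen, the protocol names no model for an arm HR at all, and the same sentence repairs that.

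A reader might also infer that the unstratified interval is too wide and that stratifying would narrow it. The calculation does not support this: the stratified interval is the same or up to about 2% wider on the log scale. The conservative SE is real only against the estimator's own sampling variation, and only if randomization was stratified by nodal status, which section 7.0 does not say.

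Third, a marginal HR is a legitimate estimand, so part of the gap is non-collapsibility and not error. That is fair. It does not remove the mismatch with a test that conditions on nodal status.

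Finally, leaving surgeon out of a 96-patient analysis is defensible: six strata cost a little precision, and no gain from adding surgeon has been shown. Nodal status is the factor that matters here.

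**Conclusion.** The point holds as a mismatch to be repaired, conditional on arm being among the Cox variables. With a true HR of 0.60, the unstratified estimate is about 0.62 at an assumed nodal HR of 2 and 0.65 at 3, against 0.60 stratified. The shift is nil when nodal status is not prognostic or the true HR is 1, so it is too strong to say that the plan's HR is always pulled toward 1. Disagreement between the Cox interval and the log-rank result at 0.05 is about 2% to 16% across nodal HRs of 1 to 3 at a true HR of 0.60, and about 1% to 3% when the true HR is 1.

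These figures rest on an assumed nodal HR, exponential survival and a 60% node-positive share; the protocol gives no survival assumptions of its own. Priority is low: OS and DFS are secondary and unpowered, the error is in the conservative direction, and the planned arm test already allows for nodal status. The conflict between section 7.0 and the other three statements of the strata stands whatever the simulation shows.

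**What to change.** In 17.2:

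- State that the arm HR and 95% CI for OS and DFS come from a Cox model stratified by the randomization factors.
- Use the same strata in the log-rank test.
- Label the univariable Cox regressions as descriptive prognostic analyses.

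Reconcile section 7.0 (surgeon only) with 5.1.3, 17.1 and the Study Schema (nodal status and surgeon), recording what was actually done, so that the strata are unambiguous. If six strata are judged too many, keep nodal status in both analyses and give the reason for leaving surgeon out.

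The cost is one or two sentences and a strata statement in the program, with no new data. Nodal strata widen the log-scale interval by 0% to 2%; adding surgeon costs a further 2% to 3% in SE.

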**3.2 Secondary Objectives**

3.2.1 To assess and compare the toxicities and morbidities of each approach.

3.2.2 To compare overall survival rates between the two treatment arms.

3.2.3 To compare recurrence in the two groups including local (gastric or esophageal bed), regional (regional lymph nodes), and distant recurrences (supraclavicular lymph node, liver, peritoneal carcinomatosis, or lung, brain, etc.).

3.2.4 To conduct an economic analysis comparing the two treatments.

3.2.5 To compare the proportion of complete (R0), microscopic positive (R1), and grossly positive (R2) resections between treatment arms.

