**7.1 Overview of Treatment Plan**

The control arm of this study will consist of induction chemotherapy (2 Cycles - Cisplatin plus continuous infusion of 5-Fluorouracil) and concurrent radiation followed by surgical resection of the esophagus. The experimental arm will consist of surgical resection followed by (if required based on final pathological staging) two cycles of chemotherapy (Epirubicin, Cisplatin and continuous infusion of 5-Fluorouracil) and concurrent extended volume radiation treatment with the last 2 cycles. Follow-up of patients with clinic visits of similar frequency to the experimental arm will be required to avoid introduction of bias in recording of time to progression.

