**8.2.5 Positive Resection Margins**

Patients that are found to have cancer positive proximal, or distal margins following preoperative chemoradiation and surgery should be considered for additional chemoradiation at the discretion of the medical and radiation oncologists. Patients in the experimental arm (postoperative chemoradiation) that were found to be T1-2 and N0 with positive resection margins should also be considered for postoperative chemoradiation.

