**10.0 RADIATION THERAPY**

Chemoradiation will be offered to patients with either pT3 or pN1 resected tumours. Resected pT1N0, pT2N0 patients will not be offered adjuvant therapy but will be followed and analyzed together in the experimental arm using the intention-to-treat principle.

Patients that haveR1 or R2 positive resection margins following induction chemoradiation will not receive adjuvant chemotherapy.

The total dose for both arms will be 50.4Gy (1.8Gy/fx/day), 5 days a week, prescribed to the periphery (95% isodose curve of the PTV.)

External Beam Equipment

Megavoltage equipment is required with effective photon energies >_ 6MV.

Treatment Planning – 3 D.

Treatment planning CT study will be required to define gross tumor volume (GTV) and

planning target volume (PTV). For this study, local regional nodes (whether clinically

positive or negative) will be included in the clinical target volume (CTV). Each patient will be positioned in an individualized immobilization device in the treatment position on

a flat table. The GTV and PTV and normal organs will be outlined on all appropriate CT

slices and displayed using beam’s eye view. Normal tissues to be contoured included both lungs, skin, heart, spinal cord, esophagus, kidneys, and liver. 4D-CT is allowed if applicable. VQ SPECT is optional. Patient immobilization is required. Patient may be placed in the supine or prone position.

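### Intention-to-treat is the only population for toxicity, so the plan cannot show how toxic the postoperative regimen is for the patients who receive it

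*Protocol*

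**What the plan says.** Section 17.2 of the protocol sets one population for everything: "All statistical analysis was intention-to-treat and performed using SAS version 9.4 software". Section 7.0 is in line with this: "all outcome events will be attributed to the study group to which the patient has been assigned".

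Exposure to chemoradiation is conditional in the experimental arm only. Section 7.1 describes that arm as "surgical resection followed by (if required based on final pathological staging) two cycles of chemotherapy" and concurrent radiation. Section 10.0 says that pT1N0 and pT2N0 patients "will not be offered adjuvant therapy but will be followed and analyzed together in the experimental arm using the intention-to-treat principle". Section 8.2.5 narrows this group: experimental-arm patients "found to be T1-2 and N0 with positive resection margins should also be considered for postoperative chemoradiation". In the control arm, sections 7.1 and 9.0 plan chemoradiation for every patient before surgery.

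Toxicity is a compared outcome. Secondary objective 3.2.1 is "To assess and compare the toxicities and morbidities of each approach", and section 11.2.4 defines the outcome as adverse drug or radiation events. Neither section names a denominator, and no section exempts toxicity from the rule in 17.2.

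**The concern.** Adverse events of a drug or of radiation depend on exposure. A rate over all randomized patients is the product of two things: how toxic the treatment is, and how many patients received it. Here the second factor differs between arms by design, because a group defined by pathology is spared chemoradiation in one arm only. Any other experimental-arm patient who does not start treatment after esophagectomy adds to that group.

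At stake is what the toxicity result can be used for. The postoperative regimen contains epirubicin and extended-volume radiation, which the control regimen lacks. A pT3 or pN1 patient offered that regimen needs the rate among patients who receive it. The plan as written yields only a rate diluted by patients who did not.

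This is more than a detail left to a statistical analysis plan. The protocol fixes the population for all analyses, so a safety set by treatment received, if defined elsewhere, would conflict with the wording of 17.2.

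**Working it through.** **Inputs from the protocol.** Two-sided alpha 0.05, SD 25, difference 15, power 80% (section 17.1); 48 per arm after the 10% allowance, allocated 1:1. The protocol gives no figure for the toxicity comparison.

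**The plan's own figure.** n per arm = (1.96 + 0.84)² × 2 × 25² / 15² = 43.6, rounded up to 44, as stated. 44 × 1.1 = 48.4, against the stated 48. I use 48 per arm.

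**Assumptions, none of them in the protocol for this trial.**
- r: toxicity rate per treated patient, taken as equal in both arms.
- u: share of the experimental arm that never starts chemoradiation.
- b: rate of recorded events in untreated patients.
- All control patients are exposed.

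**Formulas.**
- Control rate = r.
- Experimental rate over all randomized = r(1 - u) + b·u.
- Risk ratio = 1 - u(1 - b/r), which is 1 - u when b = 0.
- Among treated patients both arms show r, whatever u is.

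**Results.** The last column is the probability of p < 0.05, two-sided, from full binomial enumeration of the pooled two-proportion z test at 48 per arm.

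| r | b | u | Control | Experimental, all randomized | Risk ratio | P(p < 0.05) |
|---|---|---|---|---|---|---|
| 60% | 0 | 20% | 60% | 48% | 0.80 | 0.222 |
| 60% | 0 | 35% | 60% | 39% | 0.65 | 0.551 |
| 60% | 0 | 50% | 60% | 30% | 0.50 | 0.854 |
| 40% | 0 | 20% | 40% | 32% | 0.80 | 0.129 |
| 40% | 0 | 35% | 40% | 26% | 0.65 | 0.313 |
| 40% | 0 | 50% | 40% | 20% | 0.50 | 0.586 |
| 60% | 20% | 20% | 60% | 52% | 0.87 | 0.125 |
| 60% | 20% | 35% | 60% | 46% | 0.77 | 0.285 |
| 60% | 20% | 50% | 60% | 40% | 0.67 | 0.511 |

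Example, row 1: 0.60 × (1 - 0.20) = 0.48, and 0.48 / 0.60 = 0.80. Row 7: 0.60 × 0.80 + 0.20 × 0.20 = 0.52, and 0.52 / 0.60 = 0.87.

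The introduction quotes a 41% grade 3 rate from a gastric chemoradiation trial. Used only as an illustration, with b = 0, it gives 32.8% against 41% at u = 20% and 28.7% at u = 30%.

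**Reading.** Under these assumptions the all-randomized rate in the experimental arm lies below the rate among its treated patients whenever u > 0 and b < r. How far below depends on u, r and b.

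**The case against.** The strongest objection is that intention-to-treat answers the objective as worded. Objective 3.2.1 compares approaches, section 3.0 frames the comparators as adjuvant and induction trimodality therapy, and sparing low-stage patients is part of the adjuvant strategy. Fewer chemoradiation events for that reason are a real effect of assignment. This stands. A reader might infer from the table that the plan has a 22% to 85% chance of a false safety claim. It does not: those are chances of detecting a true difference between strategies. They would mislead only if read as a comparison of how tolerable the two regimens are.

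The size is also open to challenge, and most of this stands. The protocol gives no u. The regimens differ, so equal toxicity per treated patient is hypothetical. Toxicity and morbidity data are collected from all patients every 2 months to 1 year (section 12.1), so untreated patients can record events; with a 20% background rate the 60% case falls from 0.222, 0.551 and 0.854 to 0.125, 0.285 and 0.511. Section 17.2 names no test for toxicity and says the secondary outcomes are not powered.

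A reader might also infer a matching design flaw for operative morbidity. The documents do not support that. Surgery is planned in both arms, so dilution there would come from control patients who drop out before surgery, not from a rule. The net direction over toxicities and morbidities together is therefore not established.

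The objection that this is only a missing safety set does not stand in full. Section 17.2 states a rule for all analyses, and the rule is what needs qualifying.

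**Conclusion.** The point holds in a limited form. As the sole toxicity analysis, intention-to-treat cannot show how toxic each regimen is for those who receive it, and it understates chemotherapy and radiation toxicity for a pT3 or pN1 patient given the postoperative regimen. The cause is a design rule that applies to the experimental arm only.

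With equal toxicity per treated patient, full exposure in the control arm and no events in the untreated, the understatement is a factor of 1 - u. It is smaller with any background rate. Since u is not given, the size in this trial is unknown.

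The all-randomized comparison is not wrong and should not be replaced. The primary FACT-E analysis and the sample size are unaffected. This is a cheap improvement to a secondary outcome.

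**What to change.** Keep intention-to-treat in 17.2 for all between-arm comparisons, toxicity included. Add a sentence along these lines: in addition, chemotherapy and radiation toxicity will be summarized descriptively by assigned arm among patients who started that modality, and operative morbidity among patients operated on, with the number exposed in each arm.

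The cost is one sentence and a second denominator in the toxicity tables. It needs no change to sample size or treatment rules. Treatment characteristics are already to be described by arm under 17.2, so the numbers exposed should be at hand.

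The downside is that treated subsets are selected after randomization: postoperative starters have mainly pT3 or pN1 disease and have recovered from surgery, whereas control patients start before any such selection. The added rates are therefore descriptive, should carry no between-arm test, and should be labelled as not a randomized contrast.
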